#### F. DATA-ANALYSIS and presentation/syntheses

The effects on the primary outcomes will be evaluated using linear mixed effect models with treatment, baseline measure, and control variables (used in the sequential balancing minimization procedure; Borm et al. 2005) as covariates and Psycho-geriatric unit (PGUU) as a random effect, to correct for dependencies within PGUs. Structural Equation Modeling will be used in the secondary analysis to evaluate the plausibility of a theoretical model of causal chains of effects based on the suggested mediator variables (e.g. WIB, PE/PD). Additionally, quantitative and qualitative process analyses will be carried out in order to determine the level of use of new knowledge and skills in daily practice, and in order to determine relevant facilitators and barriers to implementing new knowledge. To that aim, checklists will be used.

#### G. ECONOMIC EVALUATION

This cost effectiveness analysis focuses on adding the DCM-intervention to nursing home Psycho-geriatric Units (PGUs) and comparing this to usual care from a societal perspective. The economic evaluation is based on the general principles of a cost-effectiveness analysis from a societal viewpoint.

Based on the above mentioned primary outcomes that vary between objects of study (residents and staff), two different incremental cost effectiveness ratios (ICERs) will be computed: Costs per quality of life (DQOL) increase (residents), and costs per increase in job satisfaction (staff). Other outcome measures such as neuropsychiatric symptoms relief (residents), work-stress and stress related absenteeism and turnover rate will be monetarized and entered in the ICER on the costs side. Finally, as a scenario, a net monetary benefit will be determined.

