**G. ESTIMATE THE POTENTIAL EFFECTS ON COSTS FROM THE INTERVENTION(S):**

The ratio behind the expected effects of our intervention on costs is the following:

1. Reduced prevalence and intensity of neuropsychiatric symptoms will have positive effects on formal caregivers by reducing their work- stress and by increasing their feeling of competence and job satisfaction.
2. This will have positive effect on productivity and efficiency of care through a reduction in job related illness, absence and turnover, and through more efficiently organized work-processes.
3. Reduced residents' care needs and negative outcomes (e.g., use of psychoactive medication, acute hospitalization or transfer to psychiatric hospitals), may directly reduce the costs of care. (3, 4, 27)

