#### E. OUTCOME PARAMETERS

- I. Residents: 1. Neuropsychiatric symptoms - primary (CMAI, NPI-NH), 2. Quality of life (WIB, Dqol) – secondary
- II. Staff: 1. Job-related stress – secondary (GHQ – short version); 2. Sense of competence – secondary (SCQ); 3. Job-stress related absenteeism, and turnover (organisational databases) -secondary; 4. Job satisfaction (MAS en VAS) - secondary;

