##### Cost analysis:

The cost analysis consists of two main parts. First, on patient level, volumes of care (to determine the incremental direct health care costs) based on the production process of the care program (with and without DCM) will be measured prospectively using an activity based costing approach. Focusing on activities performed with costs accumulated at the activity level(s) of the health care production processes, standardized case report forms will be used to assess time invested by nursing staff (including extra training), psychologist, physician, and activity therapist. Also, number of psychiatric consultations, consultations of medical specialists at hospitals, hospital admissions (number of days in hospital) and use of antidepressant as well as all other medication will be recorded. With regard to staff the costs associated with sick leave (stress related absenteeism) and turnover costs will be collected using diaries and the nursing home administration. Furthermore the DCM intervention costs will be determined. It is hypothesized that the use of the above outlined intervention results in less health care consumption (lower care needs, lower use of (psychoactive) medication, less treatments of adverse events, lower staff illness, absence and turnover rates) compared to usual care. Resident Classification Scale (RCS) (DoHA 1997)(37) will be used to determine and compare change in patients care needs and the relative resource allocation in the treatment and control group. Overall, care/service needs can be rated from A (very low) to E (very high) and ratings are used to define categories (1–8 categories). When the resident is allocated a high proportion of Cs, Ds & Es, they are rated as a Category 1 or 2, indicating high care needs, and costs.

Second, the cost prices for each volume of consumption will be determined, to use these for multiplying the volumes registered for each participating patient. The guidelines for cost analyses will be used (CVZ, Oostenbrink et al., 2004). For units of care/resources where no guideline or standard prices are available, real cost prices will be determined. As a basis for the cost price calculations for each participating unit a unique cost price, based on standardized calculation methods will be determined. This results in total costs incorporating total resident related costs and total staff costs per PGU.

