The impact of deterministic variables such as cost prices for volume parameters that are incremental cost drivers, will be investigated using sensitivity analyses on the basis of the range of extremes.

ICERs will be computed and sampling uncertainty will be determined using the bootstrap or Fieller method. Finally, a cost-effectiveness acceptability curve will be derived that is able to evaluate efficiency by different thresholds for the ICERs.

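### The economic evaluation calls two secondary outcomes primary, plans no ratio on the declared primary outcome, and lets symptom and stress benefits be counted twice on the cost side

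*Protocol*

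**What the plan says.** Protocol, Strategy, section E (Outcome parameters) ranks the resident outcomes as "Neuropsychiatric symptoms - primary (CMAI, NPI-NH), 2. Quality of life (WIB, Dqol) – secondary". It lists every staff outcome, including job satisfaction, as secondary. The Objective gives the same ranking.

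Section G (Economic evaluation) then starts from a different ranking: "Based on the above mentioned primary outcomes that vary between objects of study (residents and staff), two different incremental cost effectiveness ratios". It names the two ratios as "Costs per quality of life (DQOL) increase (residents), and costs per increase in job satisfaction (staff". In the next sentence symptom relief, work-stress, stress-related absenteeism and turnover are grouped as other outcomes, which "will be monetarized and entered in the ICER on the costs side". The only further summary is a net monetary benefit, presented as a scenario.

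The Cost analysis that follows records staff time, psychiatric and specialist consultations, hospital stays and all medication for residents. For staff, "the costs associated with sick leave (stress related absenteeism) and turnover costs will be collected using diaries and the nursing home administration".

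**The concern.** Two things look wrong.

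First, the economic section works from an outcome hierarchy that the rest of the protocol contradicts. The only reason it gives for choosing its two effect measures is that they are primary, and they are not. The outcome that is primary, and on whose CMAI score the trial is sized, has no cost-effectiveness ratio.

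Second, a cause and its consequences are placed side by side in the numerator. If fewer symptoms and less stress are worth money because they reduce absence, turnover and care use, and those reductions are already costed, a separate money value for symptoms and stress adds some of the same benefit again.

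Cost-effectiveness is in the trial's title and main objective, so both the size and the sign of the base-case result are at stake. The acceptability curve and the net monetary benefit would carry the same error.

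**Working it through.** The protocol gives no figure to reproduce here, so the check compares its sections.

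**Step 1: the label.**

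| Outcome | Section E and Objective | Section G (Economic evaluation) |
|---|---|---|
| Neuropsychiatric symptoms (CMAI, NPI-NH) | primary | other outcome, moved to the cost side |
| DQoL | secondary | effect measure, called primary |
| Job satisfaction | secondary | effect measure, called primary |

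Section G speaks of primary outcomes for both residents and staff. No staff outcome is primary in section E, the Objective or the summary. The two rankings cannot both be right.

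**Step 2: the ratios.** Section G and the Cost analysis plan two ratios, an acceptability curve and a scenario net monetary benefit. None is expressed per CMAI or NPI-NH unit.

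**Step 3: the overlap.** The rationale is under Relevance, in the section estimating effects on costs. It says that fewer and milder symptoms reduce work-stress and raise job satisfaction, and that this improves productivity "through a reduction in job related illness, absence and turnover". It adds that lower care needs and fewer adverse outcomes, such as psychoactive medication and hospitalisation, may reduce costs directly. Against this chain:

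| Link in the chain | Costed in the Cost analysis | Also monetised in section G |
|---|---|---|
| Symptom relief | no separate entry | yes |
| Work-stress | no separate entry | yes |
| Absence, turnover | yes | yes (read as the same entry) |
| Care use, medication, admissions | yes | not listed |

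The staff-side links are explicit. The resident-side link is implied, because care needs and adverse outcomes stand in the same list without being tied to symptoms in so many words. If the first two rows receive their own money value, whatever part of it reflects the last two rows is counted twice.

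**Step 4: direction and size.** The protocol gives no unit value for symptom relief or work-stress, so the actual size cannot be computed. The following uses arbitrary units, all assumed, only to show how the error behaves. Let the intervention cost 100, the absence and turnover saving be 40, the care saving be 30 and the effect gain be 1. Let f be the share of those savings that the extra money value repeats.

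ICER = [100 − 40 − 30 − f × (40 + 30)] / 1 = 30 − 70f

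- f = 0: 30
- f = 0.25: 30 − 17.5 = 12.5
- f = 0.50: 30 − 35 = −5
- f = 1: 30 − 70 = −40

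In this example the sign changes at f = 30/70 = 0.43. Beyond that, a net cost looks like a saving with a better outcome.

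**The case against.** The strongest reply concerns the word monetarized. Absenteeism and turnover appear both in section G and in the Cost analysis, and it is natural to read the second as carrying out the first. On the same reading, symptom relief and work-stress would be valued only through the care volumes, medication, sick leave and turnover that the Cost analysis records, and nothing would be counted twice. No separate price for a symptom or stress point is given anywhere. This reading is possible, and it is why the double count is stated conditionally. But the text lists symptom relief and work-stress as items in their own right and does not limit how they are valued, so a literal analyst could add them.

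It can also be said that quality of life is a legitimate effect measure, and that the Objective frames efficiency through care needs, stress, absence and turnover. Both statements are correct. A reader might infer that the stated aim is cost-effectiveness in reducing symptoms, or that CMAI must be the main ratio. The documents support neither. What stands is that the choice rests on a wrong label and that the declared primary outcome has no ratio.

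A reader might also infer that the uncertainty analysis ignores clustering and gives intervals that are too narrow. The protocol says only that "sampling uncertainty will be determined using the bootstrap or Fieller method". It names no resampling unit, and it totals costs per PGU, which is compatible with resampling whole units. That detail can be left to an analysis plan and is no fault here.

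**Conclusion.** The mislabelling is certain: section G contradicts section E and the Objective. The absence of a ratio on CMAI or NPI-NH is also plain from the text.

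The double count is conditional. It arises if symptom relief and work-stress receive a money value beyond the resources already costed, and it equals the overlapping part of that value. A reader might infer that every euro saved is counted again in full. That is only the upper limit, and the documents do not show where within the range the overlap lies. The direction is also conditional: incremental cost is understated if DCM reduces symptoms or stress, and overstated if they worsen.

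The fault is confined to the economic evaluation and does not touch the mixed-model analysis of the primary clinical outcome. It should be settled before the economic analysis is run, because the sign of the result may depend on it.

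**What to change.** In section G (Economic evaluation):

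1. Delete the word primary where it describes DQoL and job satisfaction, and refer to them as secondary outcomes used as effect measures.
2. Add an incremental cost per CMAI point alongside the two planned ratios. CMAI is the natural choice of the two primary instruments because the sample size is based on it.
3. State that the base-case cost side contains only observed resource use, sick leave and turnover, each entered once. Drop separately monetised symptom relief and work-stress from it.

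All the data are already planned, so the cost is a few sentences and a small change to the analysis. The downside is one more ratio to report and a possibly less favourable result for DCM.

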##### Cost analysis:

The cost analysis consists of two main parts. First, on patient level, volumes of care (to determine the incremental direct health care costs) based on the production process of the care program (with and without DCM) will be measured prospectively using an activity based costing approach. Focusing on activities performed with costs accumulated at the activity level(s) of the health care production processes, standardized case report forms will be used to assess time invested by nursing staff (including extra training), psychologist, physician, and activity therapist. Also, number of psychiatric consultations, consultations of medical specialists at hospitals, hospital admissions (number of days in hospital) and use of antidepressant as well as all other medication will be recorded. With regard to staff the costs associated with sick leave (stress related absenteeism) and turnover costs will be collected using diaries and the nursing home administration. Furthermore the DCM intervention costs will be determined. It is hypothesized that the use of the above outlined intervention results in less health care consumption (lower care needs, lower use of (psychoactive) medication, less treatments of adverse events, lower staff illness, absence and turnover rates) compared to usual care. Resident Classification Scale (RCS) (DoHA 1997)(37) will be used to determine and compare change in patients care needs and the relative resource allocation in the treatment and control group. Overall, care/service needs can be rated from A (very low) to E (very high) and ratings are used to define categories (1–8 categories). When the resident is allocated a high proportion of Cs, Ds & Es, they are rated as a Category 1 or 2, indicating high care needs, and costs.

Second, the cost prices for each volume of consumption will be determined, to use these for multiplying the volumes registered for each participating patient. The guidelines for cost analyses will be used (CVZ, Oostenbrink et al., 2004). For units of care/resources where no guideline or standard prices are available, real cost prices will be determined. As a basis for the cost price calculations for each participating unit a unique cost price, based on standardized calculation methods will be determined. This results in total costs incorporating total resident related costs and total staff costs per PGU.

The impact of deterministic variables such as cost prices for volume parameters that are incremental cost drivers, will be investigated using sensitivity analyses on the basis of the range of extremes.

ICERs will be computed and sampling uncertainty will be determined using the bootstrap or Fieller method. Finally, a cost-effectiveness acceptability curve will be derived that is able to evaluate efficiency by different thresholds for the ICERs.

#### H. SYSTEMATIC REVIEW

Here, we are using the existing systematic review made by our co-applicant [name] and published in 2005. (38) In addition, we will discuss studies which appeared between 2005 and 2009, separately. The purpose of this review of the research literature is to answer some key questions about the nature of the DCM-tool and its efficacy.

#### SEARCH TERMS

- Population

People with dementia residing in nursing homes.

- Intervention  
Dementia Care Mapping, DCM

- Methodological filters  
Descriptive studies and dissertations were not included

#### DATABASES USED AND NUMBER OF MANUSCRIPTS RETRIEVED

The international DCM network led by the University of Bradford maintains a DCM bibliographic database that contains all known publications on DCM (<http://www.bradford.ac.uk/acad/health/dcm>). This database formed the basis of this review. It includes refereed and nonrefereed journal articles, book chapters, theses, and non-English language texts. It is updated by the Bradford Dementia Group with Annual bibliographic searches on Medline, Cinahl, and Psychinfo using the terms 'Dementia Care Mapping' and 'DCM'. Thirty-four articles met the inclusion criteria. They were divided into five main types: (a) cross-sectional surveys, (b) evaluations of interventions, (c) practice development evaluations, (d) multimethod evaluations, and (e) papers investigating the psychometric properties of DCM.

#### RESULTS (SECONDARY OUTCOME PARAMETERS; DCM- key questions).

##### 1. DOES DCM MEASURE QUALITY OF CARE AND/OR QUALITY OF LIFE?

Concurrent validity (convergent) of WIB scores with proxy quality-of-life measures.

- Fossey and colleagues (2002) demonstrated a significant correlation between WIB scores and the Blau (1977) proxy measure of quality of life.
- Edelman and colleagues (2004) demonstrated a moderately significant correlation between WIB scores and two staff proxy measures of quality of life—the Quality of Life AD—Staff (Logsdon, Gibbons, McCurry, & Teri, 2000) and the Alzheimer's Disease-Related Quality of Life (ADRQL; Rabins, Kasper, Kleinman, Black, & Patrick, 1999) in adult day care.
- Edelman and colleagues (2004) study did not demonstrate a correlation between any of these measures compared to direct quality-of-life interviews with a less cognitively impaired subgroup.

##### 2. CAN DIFFERENT MAPPERS USE DCM RELIABLY?

- Only Fossey and colleagues (2002) looked at test–retest reliability. The best correlation was between percentage of +3 and +5, followed by overall WIB score. Significance was more moderate for type of BCC but still at an acceptable level.
- Surr and Bonde-Nielsen (2003) outline the various ways in which reliability can be achieved in routine mapping.

##### 3. DOES DCM SHOW REPRESENTATIVE RELIABILITY ACROSS ALL PEOPLE WITH DEMENTIA?

- There is evidence to suggest that level of dependency is correlated with DCM scores, specifically that low WIB scores are associated with high dependency levels. This has been demonstrated statistically on three different continents (Brooker et al., 1998; Chung, 2004; Edelman et al., 2004; Kuhn et al., 2004; Thornton et al., 2004) using three different measures of dependency.
- Brooker and colleagues (1998) found that the correlation between dependency and WIB score disappeared after three successive cycles of DCM. The authors believed that, by this stage, ways of supporting well-being of participants who were highly dependent had been better established.
- The evidence that dependency level skews DCM results is strong enough to suggest that a measure of dependency should be routinely taken alongside DCM evaluations so that the results can be scrutinized for this relationship.

##### 4. IS DCM A SUITABLE TOOL FOR RESEARCH?

- Acceptable inter-rater reliability is achievable, and concurrent validity with other proxy measures of quality of life has been demonstrated. Fossey and colleagues (2002) demonstrated internal consistency and test–retest reliability.
- What is clear is that BCCs do not measure real-time estimates of different types of behavior (Thornton et al., 2004).

#### 5. WHAT DO THE SCORES MEAN IN TERMS OF BENCHMARKING?

- Work is currently underway to develop an international database of DCM results to which all international strategic DCM partners would have access. The database should include participant and facilities factors that could be used in stratified analyses, correlational studies, and as adjustment factors.

#### 6. WHAT IS A SIGNIFICANT CHANGE IN SCORES?

- Intervention studies (Brooker & Duce, 2000; Brooker, 2001; Gigliotti et al, 2004; Jarrott & Bruno, 2003) report differences in the range of 0.4 to 1.1, which were all statistically significant. Changes in individual WIB scores, WIB value profiles, and BCC profiles are more variable. Further research is needed to clarify what constitutes a clinically significant change.

#### SUMMARY AND CONCLUSION

"These studies report evidence that DCM has a role in practice development and research within the broad aim of improving the quality of life for people with dementia. A large international database on DCM results would help clarify the relationship between DCM results, dependency, diagnostic group, and facility characteristics. Steps need to be taken through the development of the method, training, and accreditation to ensure reliability. The published work on DCM is of variable quality but is growing in strength. DCM's advantages are that it is standardized, quality controlled, international, responsive to change, multidisciplinary, and has an increasing research base. DCM provides a shared language and focus across professional disciplines, care staff, and management teams. It is seen as a valid measure by frontline staff as well as those responsible for managing and commissioning care. It also provides a shared language between practitioners and researchers. DCM holds a unique position in relation to quality of life in dementia care, being both an evaluative instrument and a vehicle for practice development in person-centered care. Maintaining a dialogue between the worlds of research and practice in health and social care is a major challenge. DCM provides an opportunity to do this. "(38)

#### NEW SEARCH; STUDIES 2005-2009

The same search was performed in PubMed on 26-01-2009. 8 studies were retrieved whereof 5 were selected as relevant. Of the remaining three studies, one was in Japanese, one was a neurological study and one concerned hospital care. To the 5 selected studies we have added a Dutch pilot study (PC) which is not retrievable from PubMed. The main findings of the in total 6 studies will be briefly summarized below.

1. "Inappropriate treatment of people with dementia in residential and day care." Objective - to investigate inappropriate treatment and its context in the care of people with dementia. Method - 85 clients across eight care units providing dementia care were observed by means of a structured Dementia Care Mapping method (DCM). Results - Of the 17 DCM categories for inappropriate treatment, withholding, invalidation, and objectification were the categories coded most frequently. Inappropriate treatment episodes were mostly associated with eating and situations in which a client had a need or request. Most episodes occurred accidentally. Conclusion - The results show that nurses involved in dementia care need more knowledge of how illnesses causing dementia change the way the affected person experiences reality, and of the ethical aspects of their work. (58)

2. "Determining the efficacy of Dementia Care Mapping as an outcome measure and a process for change: A pilot study" Report of a pilot study conducted with 35 dementia care residents in three secure residential care units in the state of New South Wales, Australia, prior to the controlled trial. Aims - To determine the sensitivity of DCM against the validated baseline and outcome measures selected for the trial and to evaluate the utility of the research plan. Results - The utility of the research plan was established. Whilst a significant improvement was shown in staff interactions with residents over time, there was no evidence that DCM improved the residents' quality of life and well-being in relation to physical and cognitive functioning. There was a reduction in the residents' levels of agitation (CMAI) and depression. While as a research tool DCM needs further refinement to match the strength of validated outcome measures that more accurately assess the residents' well-being, DCM procedures improved staff's attention to monitoring and attending to the residents' well-being. (10)

3. "Initial validation of DCM 8 in UK field trials" Objectives - To describe DCM 8 and report on the initial validation study of DCM 8.

Results - At a group score level, WIB scores and spread of Behavioural Category Codes were very similar, suggesting that group scores are comparable between DCM7 and 8. Interviews with mappers and focus groups with staff teams suggested that DCM8 was preferable to DCM 7th edition because of the clarification and simplification of codes; the addition of new codes relevant to person-centred care; and the replacement of Positive Events with a more structured recording of Personal Enhancers. Conclusions - DCM 8 appears comparable with DCM 7th edition in terms of data produced and is well received by mappers and dementia care staff. (11)

4. "Dementia care mapping as a research tool."

Review. Descriptive data from several different research teams on the distribution and psychometric properties of DCM data were compiled and summarized. Conclusions - Despite the identified limitations, DCM has promise as a research measure, as it may come closer to rating QOL from the perspective of persons with dementia than other available measures. Its utility will depend on the manner in which it is applied and an appreciation of the measure's strength and limitations. Possible changes that might improve the reliability, validity, and practicality of DCM as a research tool include coding the predominant event

(rather than the 'best' event), shortening the observation period, and adding '0' as a neutral WIB coding option. (12)

5. "Evaluating the quality of life of long-term care residents with dementia."

Review. Resident cognitive impairment, functional impairment, social withdrawal, agitation, depressive symptoms, and number of comorbid conditions had significant negative associations with WIB scores, whereas resident age, gender, and race did not. Data from the UK sample demonstrated a significant relationship between WIB scores and the Care Dependency Scale (Dijkstra et al., 2000) ( $r^2=0.35$ ;  $p<0.011$ ), with 14% of the variance in WIB scores accounted for by differences in dependency. (59)

5. "Effects of Dementia Care Mapping (DCM) on the Quality of Life of the nursing home Residents with dementia and on the job satisfaction of their formal caregivers at Psycho-geriatric Units."

Dutch pilot study investigated pre-post differences (no control group) in behaviour (GIP), agitation (CMAI), and wellbeing (PGCARS). Significant positive effects were found on Orientation (GIP,  $p<.05$ ), and verbal agitation (CMAI;  $p<.05$ ). In addition, significant changes were found in General job satisfaction (VAS;  $p<.05$ ).

